#### Eligibility

Individuals who are planning to visit Japan from the United States, the United Kingdom and Australia will be recruited by a website. They will indicate whether they are willing to participate in research online through a company. The questionnaire will be in English only to prevent biases regarding interpretation. Individuals who are 18 years old or older, understand English, and have previously visited or wish to visit Japan will be considered eligible to ensure the validity of the responses to our questionnaire. We will consider individuals who are interested in the health care services in Japan.

#### Enrolment procedure

We will allocate the participants to either an intervention group or a control group randomly through the Macromill Company services. The participants in this study will be screened by monitors through an online questionnaire. The participants will be able to access the survey site and to receive e-mail notices. The monitors will determine who is enrolled in our study. At the beginning of the questionnaire, the target conditions are explained, and the questionnaire is designed so that only those who meet the conditions stipulated by our research can complete the questionnaire.

The participants will be asked about their satisfaction with the Japanese health care system and health information. We will repeat this procedure until we reach our required sample size. We will also ask them to answer the questions based on their current knowledge and to not search for answers by accessing other websites or references. Each participant will receive a one U.S. dollar, one Australian dollar or one Euro gift certificate from Macromill Company upon completion of the eligibility survey in March 2021.

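### The qualifying conditions are explained at the start of the questionnaire that applies the eligibility gate, and the gift is tied to an ambiguous eligibility survey, which weakens a gate resting on self-report

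*Protocol article*

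**What the plan says.** The Eligibility section of the protocol article gives the criteria: "Individuals who are 18 years old or older, understand English, and have previously visited or wish to visit Japan will be considered eligible". It adds a subjective one: "We will consider individuals who are interested in the health care services in Japan". It also gives the purpose of the criteria: people who meet them "will be considered eligible to ensure the validity of the responses to our questionnaire".

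The Enrolment procedure section describes how the criteria are applied:

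- Screening: "The participants in this study will be screened by monitors through an online questionnaire".
- Decision: "The monitors will determine who is enrolled in our study".
- Disclosure: "At the beginning of the questionnaire, the target conditions are explained".
- Gate, in the same sentence as the disclosure: "the questionnaire is designed so that only those who meet the conditions stipulated by our research can complete the questionnaire".
- Payment: each participant receives a one-unit "gift certificate from Macromill Company upon completion of the eligibility survey in March 2021".

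Recruitment is repeated until the required sample size is reached. Sample size is 1002, for a difference of 0.178 with a standard deviation of 1.0, alpha 0.05 and 80% power. The primary outcome is the CSQ-8 score immediately after the interventions (Outcomes section).

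**The concern.** The criteria are there to protect the validity of the answers, and a gate that works on declared answers protects it only if the member does not know which answers open it. Here the stated order is explanation first and answers second. A paid panel member with little interest in Japan can learn what keeps them in and answer accordingly. Because recruitment continues to a fixed total, each such person takes the place of a genuine visitor or would-be visitor.

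Two things are at stake. If these participants attend less to the material, the difference between game and animation is diluted. And the result describes the intended population less well.

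The gift sentence is a second weakness in the same section. The primary outcome is measured after the intervention, yet the payment is attached to the eligibility survey.

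**Working it through.** **Order of events.** Set side by side, the statements in the Enrolment procedure section give this picture:

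1. The gate is part of the questionnaire, and that questionnaire opens by explaining the target conditions. Disclosure and gate stand in one sentence and refer to one instrument, so the order holds whether that instrument is a separate screener or the trial questionnaire.
2. The only input described for the monitors' decision is an online questionnaire. No other source is described.
3. Past visit, wish to visit and interest in Japanese health care services are statements by the member. The panel company may hold a record of age, but the article does not say that it is used, and a wish or an interest can come from nowhere else.

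The gate can therefore act only on declarations made after the conditions are known.

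**The gift.** The term eligibility survey has two possible meanings:

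| Meaning | Effect of the payment rule |
|---|---|
| The screener alone | Payment is earned before the intervention and gives no reason to finish the post-intervention CSQ-8 |
| The whole gated questionnaire | Payment depends on passing a gate whose conditions were just disclosed |

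These are alternatives and do not add up. Each needs a correction.

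**The plan's own sample size.** Inputs from the Sample size section: difference δ = 0.178, SD σ = 1.0, α = 0.05, power 80%. Two-sided testing and 1:1 allocation are assumed, as neither is stated.

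n per arm = 2σ²(z₀.₉₇₅ + z₀.₈₀)²/δ² = 2 × (1.960 + 0.842)²/0.178² ≈ 495.4, rounded up to 496, so 992 in total. With the noncentral t distribution it is 497 per arm, 994 in total. The stated 1002 is reproduced to within about 1%. A one-sided test would need 782 and does not reproduce it.

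At 501 per arm, SE = √(2/501) = 0.0632 and power = Φ(0.178/0.0632 − 1.960) = 80.4%. There is almost no reserve.

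**Illustration of dilution.** Let f be the share of participants who qualified falsely. Assume that they show no difference between arms, that f is the same in both arms, and that the SD is unchanged. The expected difference becomes 0.178 × (1 − f), and power = Φ(0.178(1 − f)/0.0632 − 1.960).

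| f (assumed) | Difference | Power at 501 per arm | Total for 80% power |
|---|---|---|---|
| 0 | 0.178 | 80.4% | 992 |
| 5% | 0.169 | 76.3% | 1098 |
| 10% | 0.160 | 71.8% | 1224 |
| 20% | 0.142 | 61.6% | 1550 |
| 30% | 0.125 | 50.5% | 2024 |

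The article gives no value for f and no support for the zero-difference condition. The table shows sensitivity and predicts nothing.

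**The case against.** The best case for the plan has five parts.

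1. **Timing.** The text says questionnaire, not screener, and does not clearly separate the two. A reader might infer that members are told the conditions before a distinct screening survey, but the article does not say so. This stands. What survives is narrower: whichever instrument applies the gate opens with the conditions.
2. **Safeguards.** The plan states two, a completion gate and monitors who decide enrolment. It would be wrong to read it as having none, and a journal article may leave their operating details to the full protocol. This stands too. The point is not that detail is missing. It is that the stated order undercuts the stated gate.
3. **Criteria.** They are broad, and a wish or an interest is self-declared under any screener. Neutral questions verify nothing, and the number of truly ineligible members may be small. That is correct. Neutral questions do, however, remove the cue, which is the part the plan controls.
4. **Incentive.** The sum is one dollar or one euro, and payment for completing a screener whatever its result gives no reason to answer falsely. Payment at the end could keep a false qualifier in. This is fair, and it is why the change in payment should go together with the neutral screen.
5. **Size.** The 10% and 20% shares are assumptions, and an uninterested adult might still rate a quiz game and an animation differently. This stands.

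**Conclusion.** The point holds in a limited form. The article fixes an order in which the conditions are explained at the start of the instrument that applies the gate, while the criteria as described rest on self-report. This weakens the gate. The payment sentence is badly fixed on either meaning of eligibility survey.

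The likely harm is dilution and weaker generalisability. A reader might infer a biased comparison, but the documents do not support that: random allocation should spread false qualifiers over both arms. Nor do they support any particular rate of false qualification. The fall in power from about 80% to 72% (10% share) or 62% (20% share) depends on an assumed share, on no arm difference among these participants, on an unchanged SD, and on two-sided 1:1 testing with 501 per arm.

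The change is worth making because it is nearly free and the sample size has almost no margin, not because a loss of a given size has been shown.

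**What to change.** In the Enrolment procedure section:

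- Put neutral screening questions before the target conditions are explained, worded so that they do not show which answers qualify. For example, ask which of several destinations the member has visited and which they wish to visit, with Japan as one option.
- Apply the existing completion gate to those answers.
- Bar re-entry from the same panel account, so that a member who is screened out cannot return with different answers.
- Replace the eligibility survey as the trigger for the certificate with completion of the post-intervention questionnaire.

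The position of study information and consent need not change. The consent pages are not part of the material reviewed, so that sequence cannot be judged.

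The cost is reordering and rewording an online form before launch, with no extra study procedures and no change to the planned 1002. The small downside is a somewhat lower qualifying rate, so more panel members may have to be approached.

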### Participants

#### Sample size

In this study, we expect to recruit 1002 participants via a Macromill internet panel. In the sample size calculation, a 95% confidence level and 80% power were used to detect a difference of 0.178 in the questionnaire score, with a standard deviation of 1.0, extra parameter of 0.0 and alpha of 0.05.

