### Interventions

#### Intervention

The intervention group will watch a five-minute digital game titled *Sa-Chan Game* in English (Table 1). This animation is in the format of a quiz that aims to provide information on the health care system and safety in Japan for overseas visitors. Its content is based on the results of a previous study on overseas visitors’ concerns about visiting Japan [14]. It starts with Asian music and contains 11 items. We will share the animated game through a website.

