### Outcomes

The primary outcome of this study is the difference in the average or median CSQ-8 (8-item Client Satisfaction Questionnaire) [29] score between the participants who will have played the *Sa-Chan* game and controls immediately after the interventions. We will assess the outcome using a self-administered questionnaire, the CSQ-8 scale, which has been used widely for health education [29] and has been shown to have reliable and valid in previous research [30]. The CSQ-8 is an eight-item questionnaire that uses a four-point Likert scale and will be used to assess the respondent’s level of satisfaction regarding the health care system and safety in Japan. The total score ranges from 8 to 32. A high score denotes greater satisfaction. The reliability of the questionnaire will be examined by Cronbach’s alpha.The second outcome of the study is the difference in motivation between the participants who will have played the *Sa-Chan* game and the controls immediately after the interventions. We will ask one question, “Are you likely to follow this information yourself”, and the participants will respond using a four-point Likert scale to determine whether they will change their behaviour or assess their level of motivation to follow the Japanese health-related guidelines. We will collect the data before and after the interventions. We will evaluate the data with the Information-Motivation-Behavioural Skills model [31]. This model has been used in a number of risk reduction behaviour studies [32].The third outcome is whether the participants understood the information presented in the *Sa-Chan* game. When a participant understands the information corresponding to each of 15 items, he or she will respond with “yes” to the item. The questions will be related to both interventions. If a participant understands how to deal with the following topics in Japan, he or she might choose correct answers.

In total, the questionnaire that will be used to assess the outcomes in (1), (2), and (3) and performing the intervention will take less than 10 min to complete. The participants will be visitors or individuals who wish to visit Japan.

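### Enrolment refills to a target without saying whether the 1002 counts randomised or completed participants, and the stated reward falls due before the primary outcome

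*Protocol article*

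**What the plan says.** Under Sample size the protocol article states "we expect to recruit 1002 participants via a Macromill internet panel". The calculation is described as "a 95% confidence level and 80% power were used to detect a difference of 0.178 in the questionnaire score". The other inputs listed there are alpha 0.05 and an SD of 1.0. No dropout allowance is mentioned.

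Under Enrolment procedure, the panel company performs the randomisation: "We will allocate the participants to either an intervention group or a control group randomly through the Macromill Company services". The section then covers screening by monitors and asking participants about their satisfaction, and continues: "We will repeat this procedure until we reach our required sample size". The same section describes the reward as a "gift certificate from Macromill Company upon completion of the eligibility survey in March 2021".

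Under Outcomes, the primary comparison is of the CSQ-8 between game players and "controls immediately after the interventions". Under Interventions, the game lasts five minutes and the text says of it "This animation is in the format of a quiz". The control is a four-minute animation. Both are delivered through a website in the same way and both contain 11 items.

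**The concern.** The primary outcome is a satisfaction score collected after exposure, online and unsupervised. Anyone who closes the page after allocation leaves no post-intervention CSQ-8. Two stated rules bear on this.

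First, the repeat-until-full rule does not fix its unit. The procedure to be repeated includes asking about satisfaction, so the panel company could reasonably count completed questionnaires and keep inviting people until it has 1002. Quitters after randomisation would then be refilled, and two full arms would conceal how many were lost and from which arm.

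Second, the reward as worded is earned at the eligibility survey, so it gives no reason to stay until the outcome is recorded.

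The arms also place different demands on the participant, so unequal quitting is foreseeable. If quitting is also related to satisfaction, the comparison among finishers is no longer the randomised one. Replacement does not create that bias, since losing the quitters' outcomes does so with or without refilling. Replacement hides it, and if the platform has not logged quitters by arm, no later analysis can recover the information.

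**Working it through.** **Inputs from the document.** Total 1002, difference 0.178, SD 1.0, alpha 0.05, power 80% (Sample size). Two-sided testing and 1:1 allocation (501 per arm) are assumptions, because neither is stated.

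**Reproducing the sample size.** n per arm = 2(1.960 + 0.842)² / 0.178² = 495.5, rounded up to 496, or 992 in total. With 501 per arm, SE = √(2/501) = 0.0632 and power = Φ(0.178/0.0632 − 1.960) = 80.4%. A one-sided calculation gives 782 and does not match. So 1002 reproduces as a two-sided figure, with (1002 − 992)/992 = 1% to spare. There is no real dropout allowance. That fits a count of completers but does not prove it.

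**Bias model (all quit rates and correlations are assumed).** Let d₁ and d₀ be the proportions quitting in the game and control arms, and ρ the correlation between the tendency to quit and low satisfaction. For a normal score with SD 1.0 and no true effect:

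bias = ρ [φ(z_d₁)/(1 − d₁) − φ(z_d₀)/(1 − d₀)]

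The term φ(z_d)/(1 − d) is 0.0494 at 2%, 0.1086 at 5%, 0.1950 at 10% and 0.3500 at 20%. Two-sided type I error is Φ(−1.96 + bias/SE) + Φ(−1.96 − bias/SE), with 501 analysed per arm and the SD held at 1.0.

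Examples: at 5%/2% and ρ = 0.3, bias = 0.3 × (0.1086 − 0.0494) = 0.018. At 20%/10% and ρ = 0.5, bias = 0.5 × (0.34995 − 0.19500) = 0.077.

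| Quit rate, game / control | ρ | Bias (SD) | Share of 0.178 | Type I error |
|---|---|---|---|---|
| 10% / 10% | any common value | 0 | 0% | 5% |
| 5% / 2% | 0.3 | 0.018 | 10% | 5.9% |
| 10% / 5% | 0.3 | 0.026 | 15% | 7.0% |
| 20% / 10% | 0.3 | 0.046 | 26% | 11.4% |
| 10% / 5% | 0.5 | 0.043 | 24% | 10.5% |
| 20% / 10% | 0.5 | 0.077 | 44% | 23% |
| 5% / 0% | 1 | 0.109 | 61% | 41% |
| 10% / 0% | 1 | 0.195 | 110% | 87% |

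The last two rows are extremes: nobody quits the control arm, and the game loses exactly its least satisfied users. Swapping the two arms' rates reverses the sign, so the same sizes can favour the control.

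**Cost of not replacing.** If 10% are lost in both arms, about 451 per arm remain. Then SE = √(2/451) = 0.0666 and power = Φ(0.178/0.0666 − 1.960) = 76%.

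**The case against.** A reader might infer that the plan replaces people who leave the game dissatisfied and so tilts the result toward the game. The document does not support that, for these reasons.

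- **Replacement is not stated.** The sentence sits under an enrolment heading and can mean screening and enrolling until 1002 people are in. The Sample size section speaks only of recruiting 1002. Nothing says that the count is of completers or that quitters leave the analysis.
- **Direction is not established.** No quit rates are given. The Background calls games attractive, so a passive animation might lose as many viewers or more. Nothing says that answering the quiz is compulsory.
- **The link to the score is indirect.** Outcomes describes the CSQ-8 as rating satisfaction with Japan's health care system and safety, not with the game. The Abstract and Background, however, frame the aim as satisfaction with the educational material or experience, so some link is plausible.
- **The reward sentence may be loose wording.** The text does not cleanly separate the eligibility survey from the study questionnaire, and March 2021 falls within the quarter given for the questionnaire in the Abstract.
- **There are partial safeguards.** Satisfaction is also asked before the intervention, baseline balance will be examined and regression adjustment is planned. These help but cannot remove selection on the response to the material.
- **Scope.** Analysis sets and missing-data handling may sit in a fuller document and are not faulted here.

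These points rule out a claim of demonstrated bias. They leave the stopping rule with an undefined unit and the reward tied, as written, to the wrong step.

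**Conclusion.** The point holds as a defect in two stated rules, not as a demonstrated bias. The unit of the 1002 is open, so the enrolment rule permits unseen refilling after randomisation, and the reward as worded gives no incentive to reach the primary outcome.

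The consequence cannot be computed from the document. Under the assumed normal selection model it is nil when quitting is equal and equally selective. It is about 0.02 to 0.08 SD in the moderate scenarios, from 5%/2% with correlation 0.3 to 20%/10% with correlation 0.5, and the sign depends on which arm loses more. The 0.195 SD figure, which exceeds the 0.178 target, needs one-sided and perfectly selective quitting and should be read as a bound. Because the target difference is small, even the upper moderate scenario would matter, and the change is cheap enough to make without knowing the quit rate.

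**What to change.** 1. Tie the gift certificate to completing the post-intervention questionnaire, identically in both arms.
2. Define 1002 as participants randomised, and state that nobody is replaced after allocation.
3. Have the panel platform record, by arm, the numbers randomised, started and finished.
4. Optionally, add a sensitivity analysis of the rank-sum comparison with randomised non-finishers given the lowest rank. This treats every exit as dissatisfaction and so penalises technical dropouts, which is why it belongs beside the main analysis and not in place of it.

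The first three need an instruction to the panel company. The price is somewhat fewer than 1002 completed scores, so power falls slightly below the 80.4% available at 501 per arm, to about 76% under an assumed 10% loss in both arms.

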### Interventions

#### Intervention

The intervention group will watch a five-minute digital game titled *Sa-Chan Game* in English (Table 1). This animation is in the format of a quiz that aims to provide information on the health care system and safety in Japan for overseas visitors. Its content is based on the results of a previous study on overseas visitors’ concerns about visiting Japan [14]. It starts with Asian music and contains 11 items. We will share the animated game through a website.

#### Control intervention

The control group will watch a four-minute digital animation in English named *Mari Info Japan* (Table 2). The aim is to provide information about the health care system in Japan for overseas visitors [14]. It will last for 4 min and contain 11 items in English. We will provide the digital animation in the same manner as for the intervention group though a website.

**Table 2 Tab2:**
[figure not shown]
Control group

*Mari Info Japan*: Contents of Japanese health & safety Information for international visitors

### Outcomes

The primary outcome of this study is the difference in the average or median CSQ-8 (8-item Client Satisfaction Questionnaire) [29] score between the participants who will have played the *Sa-Chan* game and controls immediately after the interventions. We will assess the outcome using a self-administered questionnaire, the CSQ-8 scale, which has been used widely for health education [29] and has been shown to have reliable and valid in previous research [30]. The CSQ-8 is an eight-item questionnaire that uses a four-point Likert scale and will be used to assess the respondent’s level of satisfaction regarding the health care system and safety in Japan. The total score ranges from 8 to 32. A high score denotes greater satisfaction. The reliability of the questionnaire will be examined by Cronbach’s alpha.The second outcome of the study is the difference in motivation between the participants who will have played the *Sa-Chan* game and the controls immediately after the interventions. We will ask one question, “Are you likely to follow this information yourself”, and the participants will respond using a four-point Likert scale to determine whether they will change their behaviour or assess their level of motivation to follow the Japanese health-related guidelines. We will collect the data before and after the interventions. We will evaluate the data with the Information-Motivation-Behavioural Skills model [31]. This model has been used in a number of risk reduction behaviour studies [32].The third outcome is whether the participants understood the information presented in the *Sa-Chan* game. When a participant understands the information corresponding to each of 15 items, he or she will respond with “yes” to the item. The questions will be related to both interventions. If a participant understands how to deal with the following topics in Japan, he or she might choose correct answers.

In total, the questionnaire that will be used to assess the outcomes in (1), (2), and (3) and performing the intervention will take less than 10 min to complete. The participants will be visitors or individuals who wish to visit Japan.

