## Abstract

**Background:**

Before the COVID-19 pandemic occurred in January 2020, the number of overseas visitors to Japan had increased threefold over the last decade. To minimize the risk of health problems, visitors should be able to access information on the health care systems of the places they visit. Most short-term overseas visitors are young adults. Although they are not very likely to get sick from noncommunicable diseases, they are at high risk for injury and often experience stomach ailments, fever, or nausea when travelling. The objective of this study is to evaluate culturally and linguistically appropriate health information on preventive health behaviours and the health care system in Japan. We will examine the level of satisfaction of overseas visitors to Japan with health care-related educational materials using a five-minute digital game named *Sa-Chan Japan.*

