A digital game is an attractive way to distribute visually and culturally relevant information [23–25]. In a previous study, a digital game on insulin therapy for children with type 1 diabetes was used, and non-supervised usage of the educational game “L’Affaire Birman” was able to improve insulin titration and carbohydrate quantification results [26, 27]. Another game used by general surgery residents in classrooms showed a significant increase in short- and long-term medical knowledge that was retained, with high learner satisfaction [28]. A separate study on lecturing nursing students showed that an educational game was both liked and accepted by the students and considered a satisfying teaching technique [16].

Digital games can also be used to share information on travel health with overseas visitors. In this research, we will evaluate the effect of a five-minute digital game titled *Sa-Chan Japan* (Table 1). We will examine the levels of satisfaction and motivation of overseas visitors to Japan regarding their educational experience.

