## Methods

### Study design and procedures

We will conduct this randomized controlled trial to examine the efficacy of an animation game in improving both satisfaction and behavioural changes among current and potential visitors to Japan. The participants will complete the survey online. The participants will answer a questionnaire on the satisfaction and behavioural changes prior to and after participating in one of two interventions. We will evaluate the changes in their satisfaction and motivation levels (Fig. 1).

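### The protocol names different objects for the primary CSQ-8 rating: the educational material in the objective, Japan's health care system and safety in the outcome definition

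*Protocol article*

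**What the plan says.** All references are to the protocol article.

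- **Abstract, Background:** the trial will examine the "level of satisfaction of overseas visitors to Japan with health care-related educational materials".
- **Background, last paragraph:** it will examine the "levels of satisfaction and motivation of overseas visitors to Japan regarding their educational experience".
- **Enrolment procedure:** "The participants will be asked about their satisfaction with the Japanese health care system and health information".
- **Outcomes:** the primary outcome is "the difference in the average or median CSQ-8 (8-item Client Satisfaction Questionnaire") score between arms immediately after the interventions. The same section says that the CSQ-8 is to measure the "level of satisfaction regarding the health care system and safety in Japan".
- **Eligibility:** adults who understand English and "have previously visited or wish to visit Japan will be considered eligible".
- **Study design and procedures:** participants complete a "questionnaire on the satisfaction and behavioural changes prior to and after participating in one of two interventions". Data analysis then plans signed-rank and rank-sum tests on the CSQ-8 scores from before and after.

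The Methods paragraph of the Abstract names the CSQ-8 without saying what is rated, so it does not settle the matter.

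**The concern.** A satisfaction score means nothing until one knows what is being rated. Here the objective names one object, the outcome definition another, and the enrolment text a mixture of the two. The trial compares a quiz game with an animation, and both carry information about health care in Japan. Its question is which format is the better educational tool.

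If the Outcomes section is followed literally, respondents rate the health care system and safety in Japan. A difference between arms would then be a difference in opinion of the system, and the absence of one would not show that the two formats are equally satisfying. The two constructs can even move in opposite directions. The Background says visitors worry most about medical costs, language and informed consent. Clear, accurate teaching on those points could lower a person's opinion of the system and still be good education.

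People who only wish to visit Japan may have no experience of the system on which to base a rating. This cannot be repaired once the responses are in.

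**Working it through.** **1. The sample size, for completeness.** Sample size gives a difference of 0.178, SD 1.0, alpha 0.05, power 80% and 1002 participants. Two-sided testing and 1:1 allocation are assumed, since neither is stated.

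- n per arm = 2 × (1.960 + 0.842)² × 1.0² / 0.178² = 15.70 / 0.03168 ≈ 495.5, rounded up to 496, or 992 in total. This is close to 1002.
- Power at 501 per arm = Φ(0.178 × √(501/2) − 1.96) = Φ(0.857) ≈ 80.4%.

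The planned size is reproduced. It neither supports nor refutes this point, which concerns what the score means.

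**2. The sections side by side.**

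| Section | Object of satisfaction |
|---|---|
| Abstract, Background | Educational materials |
| Background | Educational experience |
| Enrolment procedure | Health care system and health information together |
| Outcomes (defines the primary measure) | Health care system and safety in Japan |

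The first two rows agree. The last row differs from them, and the third straddles both. No other section reconciles them.

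**3. Can the mixture be the intended construct?** Only one total score, from 8 to 32, is planned. If respondents are free to rate either the system or the information, that total cannot be assigned to one of them.

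**4. What the before-and-after design implies.** There are two cases.

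- *The material is rated.* Nobody can rate it before seeing it, so there is no true baseline and a change score has no meaning. A baseline question about information already held rates a different object. It can help as a covariate, but it cannot be subtracted.
- *The system is rated.* A baseline exists and change can be computed, but the score is not the one the objective asks for.

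The objective and a CSQ-8 change analysis therefore cannot both be kept. The primary outcome in Outcomes, a comparison between arms immediately after the interventions, needs no baseline and fits the first case.

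**The case against.** The strongest reply is that Outcomes uses shorthand. The Intervention section describes the game as conveying information on the health care system and safety, almost the same phrase, so Outcomes may mean satisfaction with information on that topic. Outcomes also says the CSQ-8 is widely used in health education, and Enrolment procedure mentions health information. Item wording is commonly left to the full protocol. This stands in part: the questionnaire as fielded may already ask about the information. It does not remove the point, because the article does not leave the referent unstated. It states one, and that one differs from the objective.

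Three stronger readings are tempting, and the documents do not support them.

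- *That the primary outcome certainly fails to answer the trial's question.* This would require the item stems, which are not shown. It holds only for the outcome as written.
- *That a short animation cannot move a rating of the health care system.* Satisfaction is a perception, and information can shift it without any change in the system. The problem is the mismatch with the objective, not that the rating cannot move.
- *That people who have never visited dilute the effect and cost a calculable amount of power.* The documents give neither their share nor any reason to suppose that they show no effect. With little else to go on, they might respond more strongly. Nor does a previous visit imply use of health care, so visit history does not identify who can rate it. No power-loss figure is justified.

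**Conclusion.** The point holds as an inconsistency about what the primary outcome rates. Taken as written in Outcomes, the primary score does not match the objective in the Abstract and Background, and some eligible respondents may have no experience of the thing they are asked to rate. What is at stake is the interpretation of the main result. Its size cannot be put as a number from these documents.

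The conclusion rests on reading Outcomes literally and on taking the comparison of two educational formats as the trial's question. If the fielded items already refer to the information, correcting the text and the conflict with the change analysis remain. The change should be made: it is cheap before data collection and impossible afterwards.

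**What to change.** Before the online form goes live:

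1. Set one referent for all eight CSQ-8 items, the health information or material received, worded identically in both arms. Make Abstract, Background, Enrolment procedure and Outcomes agree on it.
2. Let the post-intervention comparison between arms, already named as primary in Outcomes, carry the inference.
3. Use any rating taken beforehand, for example of the information a person currently holds, only as a covariate. Do not form a CSQ-8 change score. Amend Data analysis to match, along with the statements on change in satisfaction in the Abstract and in Study design and procedures.
4. If a rating of the health care system itself is wanted, keep it as a separate secondary or descriptive item.

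The cost is rewording the item stems. Earlier validity data will apply less directly to adapted stems, although the Cronbach's alpha check already planned will cover reliability. The CSQ-8 pre/post change analysis is given up. Neither change needs more participants.
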